### 2.6. Statistical Analysis

The size and statistical power of the sample will be calculated using the G*Power software application [35]. The following parameters will be considered: F test (ANOVA); effect size: 0.25; α-level: 0.05; statistical power: 0.95; number of groups: 4; number of measures: 2 (pré and post intervention); a 30% margin for possible losses and refusals. Therefore, the initial size of the total sample was estimated at 76 participants.

The collected data will be subjected to descriptive statistical analysis where values such as maximum, minimum, mean and standard deviation will be calculated for each variable in each assessment moment. Afterwards, data normality will be tested by considering the response to three conditions: z-values from Skewness and Kurtosis tests; *p*-value from Shapiro-Wilk test; and visual inspection of generated histograms. Parametric data will be analyzed using the Student’s *t*-test for independent samples to compare the groups and two paired samples to compare the different moments (M1 and M2). Nonparametric data will be analyzed using the Mann–Whitney U test to compare the groups and the Wilcoxon test to compare the different moments (M1 and M2). Statistical analysis will be performed using the Statistical Package for the Social Sciences (SPSS) statistical software, version 25.0. The level of significance used will be *p* ≤ 0.05.

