## 3. Expected Results/Discussion

The main aim of this study is to assess the impact of different aquatic exercise programs (a continuous aerobic program, aerobic interval program and combined program) on risk markers of cardiometabolic diseases in older people. The study is guided by scientific-based evidence on the practice of physical exercise in the elderly population [11,36].

The practice of regular physical exercise is considered as the optimum tool in the prevention and treatment of various types of cardiometabolic diseases. Thus, it is important that research on this topic continues; by doing so, new intervention methods can be identified and their efficacy validated. The offer of aquatic physical exercise programs is highly successful among the elderly because they transform physical exercise into something more pleasant and suitable for this particular population. However, the high costs of maintaining aquatic environments and the additional difficulties associated with assessment methodologies and specific equipment needed to monitor exercise in aquatic environments, means this topic not yet been sufficiently explored in the literature.

After completion of the data collection and analysis, the participants in the experimental groups are expected to show positive developments with regard to the anthropometric level, physical function, the intima-media thickness of the carotid arteries, heart rate variability, cognitive function, mental health and a number of biochemical markers. It is also expected that statistically significant differences will be found between the exercise groups for some of the variables. In the control group, no changes are expected in the analyzed variables. It is believed that the expected results can be attributed to the physical and physiological effects of the aquatic environment associated with the different proposed exercise protocols. The results will be published after the study is completed.

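### Section 2.6 specifies no comparison of change, or of baseline-adjusted M2, across the four groups, although the study was sized on a four-group, two-measure ANOVA

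*Protocol article*

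**What the plan says.** Section 2.6 of the protocol article sets out the inferential scheme in two sentences. For data judged normal it plans a Student's t-test "for independent samples to compare the groups and two paired samples to compare the different moments (M1 and M2"). For other data it plans the Mann–Whitney "U test to compare the groups and the Wilcoxon test to compare the different moments (M1 and M2"). Descriptive summaries are given for each variable at each assessment moment. No change score, group-by-time term, baseline covariate, ANOVA, ANCOVA or other test spanning the four groups is named.

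The first paragraph of the same section sizes the study on a different test: "F test (ANOVA); effect size: 0.25; α-level: 0.05; statistical power: 0.95", "number of groups: 4", two measures, total 76.

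Section 2.2 forms the exercise groups from the class time for which people register. Controls are recruited separately from people who took no exercise in the past year. Section 3 expects favourable change in the exercise groups and some differences between those groups, and says "In the control group, no changes are expected in the analyzed variables". It then attributes the expected results to the aquatic environment and the exercise protocols.

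**The concern.** The aim is the effect of different programmes, so the quantity of interest is a between-group difference in change, or in M2 given M1. A paired test within one group does not estimate this. It mixes any programme effect with practice on repeated tests, season and regression to the mean. That one group reaches significance and another does not is no evidence that the two differ.

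A two-sample test on M2 alone is a between-group comparison, but it takes equal baselines for granted. With groups formed by registration and controls recruited separately, that cannot be assumed. Two-sample tests also give no joint test of four groups, and Section 2.6 states no multiplicity rule for the six possible pairs.

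The scheme applies to every outcome, so the main conclusion on each one is affected.

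**Working it through.** **1. The plan's own figure.** Inputs from Section 2.6: f = 0.25, α = 0.05, power 0.95, k = 4 groups, m = 2 measures. The correlation ρ between M1 and M2 is not stated; 0.5 is assumed.

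Group-by-time interaction: λ = f²·N·m/(1−ρ), df₁ = (k−1)(m−1) = 3, df₂ = (N−k)(m−1) = N−4.

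- N = 72: λ = 0.0625 × 72 × 2/0.5 = 18; power 0.948
- N = 76: λ = 0.0625 × 76 × 2/0.5 = 19; power 0.959

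In multiples of four, 76 is the smallest total that reaches 0.95. This is before any of the 30% margin for losses that the section mentions. The match depends on ρ: the interaction needs 104 at ρ = 0.3 and 48 at ρ = 0.7. It is also not unique, since a test of the time main effect at ρ = 0.3 gives 76 as well (power 0.953). The mismatch itself needs no assumption: the sizing names an ANOVA on four groups and two measures, and the analysis names none.

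**2. How often the misleading pattern would appear.** Assumptions not in the document: equal groups of 76/4 = 19, and the same true change of d SDs of change in all four groups, so no programme effect. Let p be the power of one two-sided paired t-test (noncentral t, 18 df, noncentrality d√19). The chance that at least one of three exercise groups is significant while control is not is (1−p)·[1−(1−p)³].

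| d | p | chance of the pattern |
|---|---|---|
| 0 | 0.050 | 0.135 |
| 0.2 | 0.131 | 0.299 |
| 0.3 | 0.236 | 0.423 |
| 0.4 | 0.379 | 0.472 |
| 0.5 | 0.541 | 0.415 |
| 0.6 | 0.696 | 0.295 |
| 0.8 | 0.909 | 0.091 |

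For d = 0.5: 0.459 × (1 − 0.459³) = 0.415. Section 2.2 reports that 102 people agreed to take part. With about 25 per group (102/4 = 25.5), the chance is 0.461 at d = 0.3, 0.445 at 0.4 and 0.318 at 0.5.

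**3. What baseline adjustment gains.** Relative to a comparison of M2 alone (variance 1), a change score has variance 2(1−ρ) and ANCOVA 1−ρ². The effect is 0.5 SD of M2, with 19 per group, two-sided α = 0.05, and ρ assumed.

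| ρ | ANCOVA variance | power, M2 only | power, change score | power, ANCOVA |
|---|---|---|---|---|
| 0.5 | 0.75 (cut 25%) | 0.32 | 0.32 | 0.41 |
| 0.7 | 0.51 (cut 49%) | 0.32 | 0.49 | 0.56 |

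**4. Pairwise testing.** Six unadjusted two-sample t-tests at 0.05 among four groups of 19 have a simulated familywise error of about 0.20 per outcome when no groups differ.

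**The case against.** The strongest reply is that the two-sample test is said only to compare the groups, with no variable named. Applied to M2 minus M1, it would be a valid comparison of change for two groups, equivalent to a 2×2 group-by-time test. A reader might infer that the plan rules out any comparison of change. The text does not support that; it supports only that no such comparison is specified. This part of the reply stands. Even on that reading, there is no joint four-group test and no multiplicity rule.

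Second, a reader might infer that the plan adopts significance in one group and not in another as its criterion. It does not: between-group tests are planned, and the sentence on controls in Section 3 is an expectation, not a decision rule. But the differences Section 3 expects between groups are among the exercise groups, and the step from expected change to attribution needs an exercise-versus-control contrast that Section 2.6 does not define.

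Third, the probabilities in step 2 rest on chosen inputs: a common change for which the article gives no basis, and equal groups. They should not be read as a false-positive rate for the trial, because the pattern becomes an error only if it is taken as the conclusion.

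Fourth, the ANOVA sizing suggests that a four-group analysis may have been intended, so the two paragraphs may simply never have been reconciled. That is plausible, and it makes the correction easier. An article may condense a fuller plan, but this one names its tests, and those are not the tests the sizing implies.

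**Conclusion.** The point holds as a defect in what is specified. Section 2.6 fixes two-sample and paired tests and no comparison of change, or of baseline-adjusted M2, across the four groups. This contradicts its own sizing basis. Followed as written, it can lead to wrong conclusions on any outcome.

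The sizes are illustrative. With 19 per group and a shared true change of 0 to 0.8 SD, the pattern of an exercise group significant and control not arises with a probability of about 9% to 47%, peaking near 0.4 SD. Adjusting for M1 cuts variance by 25% or 49% against M2 alone, at assumed correlations of 0.5 and 0.7. Against change scores the power gain is smaller (0.32 to 0.41, and 0.49 to 0.56). The contradiction with the sizing depends on none of these assumptions; only the reproduction of 76 depends on ρ = 0.5.

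**What to change.** Replace the testing scheme in Section 2.6 with one four-group model per outcome: M2 on group with M1 as covariate, or a group-by-time model, which matches the sizing. For each outcome:

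- Report the 3-df group test, then pre-specified contrasts (each programme versus control, and between programmes) as differences with 95% confidence intervals, under a stated multiplicity rule.
- Report within-group change as description only.
- For skewed or bounded outcomes, such as biomarkers, MMSE or GDS, use a suitable transformation or a rank-based or robust version of the same model.
- State that, because allocation to control is not random, adjustment removes only the measured baseline difference. Exercise-versus-control contrasts stay open to confounding, and with non-equivalent groups ANCOVA and change-score results can disagree.

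The cost is one rewritten paragraph. It needs no new data or participants.

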## Abstract

Cardiometabolic diseases are one of the primary causes of mortality and morbidity worldwide and sedentary lifestyles are contributing factors to these pathologies. Physical exercise has been recognized as an important tool in the prevention and treatment of these diseases. However, there are still some doubts about the efficacy of certain type of physical exercise programs for older participants. The main goal of this study is to assess the impact of different aquatic-based physical exercise programs on risk markers of cardiometabolic diseases in older people. The study group will consist of non-institutionalized individuals, within the age group of 65 or older. The sample will be randomly divided into four groups, three experimental groups (EG) and one control group (CG). Participants from the EGs will be exposed to three physical aquatic-based exercise programs for a period of 28 weeks (continuous aerobic, interval aerobic and combined). The evaluated parameters include anthropometry, physical functions, mental health, cognitive function, carotid arteries intima-media thickness, heart rate variability and biochemical markers. The results will allow an interpretation of the impact of different aquatic-based physical exercise programs on cardiometabolic diseases markers and can also be used as a tool for professionals to prescribe adequate and more efficient physical exercise programs.

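### Four groups are compared only by two-sample and paired tests at a flat 0.05, with no primary outcome among about 49 to 55 variables, so chance differences between the exercise programmes are very likely

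*Protocol article*

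**What the plan says.** The Abstract describes "three experimental groups (EG) and one control group (CG"), and lists seven outcome domains on an equal footing. The aim at the end of the Introduction refers to risk markers as a class. Neither these nor any other section singles out one variable as primary.

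Section 2.6 sizes the trial with an ANOVA F test, using "effect size: 0.25; α-level: 0.05; statistical power: 0.95; number of groups: 4" and two measures. The effect size is not tied to any variable. For the analysis, the same section uses Student's t-test "for independent samples to compare the groups and two paired samples to compare the different moments" when data are normal, and otherwise the Mann–Whitney "U test to compare the groups and the Wilcoxon test to compare the different moments". ANOVA does not reappear. The section ends with "The level of significance used will be" p ≤ 0.05, without distinguishing between variables, comparisons or time points.

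Section 3 adds: "It is also expected that statistically significant differences will be found between the exercise groups for some of the variables". The variables are not named.

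**The concern.** A two-sample test compares two groups. With four groups it has to be repeated, and each repetition at 0.05 adds its own chance of a false positive. The repetition then multiplies over several dozen variables. Without a primary outcome, nothing tells a reader in advance which of these tests carries the conclusion. An expected finding of significance on an unspecified subset of variables can be satisfied by whichever variables happen to cross the threshold.

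This matters because the Abstract says the results can help professionals prescribe more efficient programmes. A chance difference between two programmes could be read as grounds for preferring one of them.

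**Working it through.** **The plan's own figure.** Section 2.6 gives 76 participants. The repeated-measures ANOVA group-by-time interaction reproduces this if the pre–post correlation is 0.5, a value the article does not give:

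- Noncentrality: λ = f²·N·m/(1−ρ) = 0.0625 × 76 × 2/0.5 = 19.0.
- Degrees of freedom: (4−1)(2−1) = 3 and (76−4)(2−1) = 72.
- Power: 0.959. With equal groups, 76 (19 per group) is the smallest total reaching 0.95, before any allowance for losses.
- Other assumed correlations give other totals: 104 at 0.3, 60 at 0.6 and 48 at 0.7.

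On this reading the sample size rests on a single overall test that the analysis paragraph never runs.

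**Number of comparisons.** Four groups give 4 × 3/2 = 6 pairs, of which 3 are between exercise groups.

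**Number of variables (sections 2.4.3 to 2.4.9).** The article does not say which scores will be tested, so two counts are used.

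| Domain | Lower count | Higher count |
|---|---|---|
| Anthropometry | 9 | 8 (stature left out) |
| Physical function | 7 | 7 |
| MMSE | 1 | 1 |
| Mental health | 7 (one per instrument) | 13 (six CPSPP subscales, two EQ-5D parts) |
| Carotid and haemodynamic, one side | 8 | 8 |
| Heart rate variability | 1 | 1 |
| Lipid panel and glucose | 4 | 4 |
| Blood count | 0 | 1 |
| ELISA markers | 12 | 12 |
| Total | 49 | 55 |

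**One variable, no true effect.** Assumptions: two-sided tests, normal data, 76 split equally into 19 per group. If the tests were independent, the chance of at least one p ≤ 0.05 would be 1 − 0.95⁶ = 0.265 over six pairs and 1 − 0.95³ = 0.143 over three. Pairs share groups, so the true rates are lower. Simulation of the pairwise t-tests gives 0.20 over six pairs and 0.12 over the three exercise pairs, with almost no change at 13 or 25 per group.

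**All variables, no true effect: expected counts.** These averages do not depend on correlation between variables.

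- Exercise pairs: 49 × 3 × 0.05 = 7.35; 55 × 3 × 0.05 = 8.25.
- All six pairs: 49 × 6 × 0.05 = 14.7; 55 × 6 × 0.05 = 16.5.
- Paired tests within the four groups: 49 × 4 × 0.05 = 9.8; 55 × 4 × 0.05 = 11.

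With 49 variables, the false positives between exercise groups fall on about 6 variables on average (49 × 0.12).

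**Chance of at least one false positive.** This does depend on correlation, which the article does not give. Simulation with 49 equally correlated variables and 19 per group:

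| Assumed correlation between variables | Three exercise pairs | All six pairs |
|---|---|---|
| 0 | 0.999 | 1.00 |
| 0.3 | 0.98 | 1.00 |
| 0.5 | 0.92 | 0.98 |
| 0.7 | 0.71 | 0.87 |

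**The case against.** **The full protocol or the analysis plan may deal with multiplicity.** This stands in part. An adjustment method, or the handling of secondary outcomes, could sit in a document that is not shown, and its absence from the article is not the point here. But the article itself fixes two-sample tests and one significance level, so a later adjustment would have to change what section 2.6 says. The primary outcome is a protocol matter.

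**The counts are inferred.** This stands. Section 2.6 speaks of comparing the groups, not of testing every pair, and the number of variables depends on which subscales are analysed. However, section 3 expects differences among the exercise groups, and only two-sample tests are available to show them. The three exercise pairs are therefore hard to avoid, and they suffice for the point.

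**A reader might infer that false differences are certain, or that the plan would confirm its expectations almost surely even if all programmes were ineffective.** The documents do not support this. The chance falls to about 0.7 if the variables are highly correlated. Section 3 also expects favourable changes in the exercise groups and no change in controls. With 55 variables, the control group alone would show 55 × 0.05 = 2.75 false changes on average. In simulation without any true effect, the chance that exercise groups differ somewhere and controls show no significant change is only about 0.06 to 0.40 for correlation 0 to 0.7. Only the one expectation about differences between exercise groups is easily met by chance.

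**A reader might also take that sentence as a success criterion.** It is a narrative expectation. Section 2.6 sets no decision rule, and deleting the sentence would change no analysis.

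**Conclusion.** The point holds in a limited form. The article compares four groups by two-sample and paired tests at an unadjusted 0.05, runs no overall group test and names no primary outcome. If all pairs are compared and nothing works, one variable yields a false-positive difference with probability about 0.20 over six pairs, or 0.12 over the exercise pairs. Over 49 to 55 variables, about 7 to 8 false-positive tests between exercise groups are expected. At least one is very likely: about 0.7 at an assumed between-variable correlation of 0.7, rising to nearly 1 at zero correlation.

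The per-variable rates rest on two-sided t-tests with equal groups and are insensitive to group size. The range for at least one false positive rests on an assumed equal correlation between variables. The finding does not say that chance differences are certain, that section 3 as a whole would be confirmed, or that no adjustment exists in an unseen document.

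**What to change.** Before any post-intervention (M2) data are seen:

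1. Name one primary cardiometabolic marker, of the sponsor's choice, and tie the sample-size effect to it.
2. Test it at 0.05 with the overall four-group test of the ANOVA type that the sample size already assumes.
3. Follow with pairwise contrasts adjusted as a single family, for example Holm or Tukey over all six pairs. Under Holm the smallest p-value is compared with 0.05/6 = 0.0083. Comparisons with control and comparisons between programmes should not be split into two separately adjusted families: with Dunnett and Holm run separately after the F test, the familywise error reached about 0.07 in one simulated configuration.
4. Label all other variables secondary or exploratory and report estimates with 95% confidence intervals, optionally with false-discovery-rate control.
5. Reword section 3 so that significance on unnamed variables is not presented as the expected finding.

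This costs wording and minor analysis work; no data collection changes. The downside is fewer nominally significant results.

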## 3. Expected Results/Discussion

The main aim of this study is to assess the impact of different aquatic exercise programs (a continuous aerobic program, aerobic interval program and combined program) on risk markers of cardiometabolic diseases in older people. The study is guided by scientific-based evidence on the practice of physical exercise in the elderly population [11,36].

The practice of regular physical exercise is considered as the optimum tool in the prevention and treatment of various types of cardiometabolic diseases. Thus, it is important that research on this topic continues; by doing so, new intervention methods can be identified and their efficacy validated. The offer of aquatic physical exercise programs is highly successful among the elderly because they transform physical exercise into something more pleasant and suitable for this particular population. However, the high costs of maintaining aquatic environments and the additional difficulties associated with assessment methodologies and specific equipment needed to monitor exercise in aquatic environments, means this topic not yet been sufficiently explored in the literature.

After completion of the data collection and analysis, the participants in the experimental groups are expected to show positive developments with regard to the anthropometric level, physical function, the intima-media thickness of the carotid arteries, heart rate variability, cognitive function, mental health and a number of biochemical markers. It is also expected that statistically significant differences will be found between the exercise groups for some of the variables. In the control group, no changes are expected in the analyzed variables. It is believed that the expected results can be attributed to the physical and physiological effects of the aquatic environment associated with the different proposed exercise protocols. The results will be published after the study is completed.

## Figures and Tables

**Table 1 ijerph-17-08678-t001:** Characteristics of the three physical exercise programs applied for 28 weeks (continuous aerobic, interval aerobic and combined).

Program	Description	Intensity (Week 1–13)	Intensity (Week 14–28)	Exercises
Continuous Aerobic	30 min exercise aerobic (moderate intensity)	60–65% maximum HR	65–70% maximum HR	Basic hydro-gymnastics exercise, with some variations: running, bounce, kicking, pendulum jumping, skiing, twister and horse.
Interval Aerobic	10 min exercise aerobic (moderate intensity)	60–65% maximum HR	65–70% maximum HR	Basic hydro-gymnastics exercise, with some variations: running, bounce, kicking, pendulum jumping, skiing, twister and horse.
	5 min exercise aerobic (high intensity)	70–75% maximum HR	75–80% maximum HR	
	10 min exercise aerobic (moderate intensity)	60–65% maximum HR	65–70% maximum HR	
	5 min exercise aerobic (high intensity)	70–75% maximum HR	75–80% maximum HR	
Combined	15 min exercise aerobic (moderate intensity)	60–65% maximum HR	65–70% maximum HR	Basic hydro-gymnastics exercise, with some variations: running, bounce, kicking, pendulum jumping, skiing, twister and horse.
	15 min muscular strengthening exercises	2 steps 12 repetitions	3 steps 16 repetitions	Exercises with auxiliary equipment (dumbbells, pool noodles, etc.): elbow extension/flexion; shoulder extension/flexion; shoulder abduction/adduction; hip abduction/adduction; hip flexion/extension; knee flexion/extension; dorsal and plantar flexion of the ankle.
